### Safety Analyses

Safety will be assessed through the evaluation of endpoints related to adverse events, laboratory assessments, thyroid function tests, and vital signs.

Adverse event frequencies and numbers of subjects with adverse events will be summarized by system organ class and preferred term. Additional summaries will be presented by severity as well as by relationship to the Medicinal Product. Laboratory results will be summarized by incidence and toxicity grade and by change from Baseline to Week 24/Exit. Vital signs will be summarized descriptively.

### Analysis of Further Endpoints

Not applicable.

## Interim Analysis

Not applicable.

# Ethical and Regulatory Aspects

## Responsibilities of the Investigator

The Investigator is responsible for the conduct of the trial at his/her site. He/she will ensure that the trial is performed in accordance with the clinical trial protocol and with the ethical principles that have their origin in the Declaration of Helsinki, as well as with the ICH Guideline on Good Clinical Practice (ICH Topic E6, 1996) and applicable regulatory requirements. In particular, the Investigator must ensure that only subjects who have given their informed consent are included into the trial.

In 1998, the US Food and Drug Administration (FDA) introduced a regulation (21 CFR, Part 54) entitled “Financial Disclosure by Clinical Investigators”. For trials conducted in any country that could result in a product submission to the FDA for marketing approval and could contribute significantly to the demonstration of efficacy and safety of the drug (named “covered trials” by the FDA), the Investigator and all sub-Investigators are obliged to disclose any financial interest which they, their spouses or their dependent children may have in the Sponsor or the Sponsor’s product under study. This information is required during the trial and for twelve months following completion of the trial.

## Subject Information and Informed Consent

An unconditional prerequisite for a subject’s participation in the trial is his/her written informed consent. The subject’s written informed consent to participate in the trial must be given before any trial-related activities are carried out.

Adequate information must therefore be given to the subject by the Investigator before informed consent is obtained (a person designated by the Investigator may give the information, if permitted by local regulations). A subject information sheet in the local language and prepared in accordance with the Note for Guidance on Good Clinical Practice (ICH Topic E6, 1996) will be provided by the Sponsor for the purpose of obtaining informed consent. In addition to providing this written information to a potential subject, the Investigator or his/her designate will inform the subject verbally of all pertinent aspects of the trial. The language used in doing so must be chosen so that the information can be fully and readily understood by lay persons.

Depending on national regulations, a person other than the Investigator may inform the subject and sign the Informed Consent Form (ICF), as above.

Where the information is provided by the Investigator, the ICF must be signed and personally dated by the subject and the Investigator.

The signed and dated declaration of informed consent will remain at the Investigator’s site, and must be safely archived by the Investigator so that the form can be retrieved at any time for monitoring, auditing and inspection purposes. A copy of the signed and dated information and ICF should be provided to the subject prior to participation.

Whenever important new information becomes available that may be relevant to the subject’s consent, the written subject information sheet and any other written information provided to subjects will be revised by the Sponsor and be submitted again to the IRB for review and favorable opinion. The agreed, revised information will be provided to each subject in the trial for signing and dating. The Investigator will explain the changes to the previous version.

## Subject Identification and Privacy

A unique subject number will be assigned to each subject at inclusion, immediately after informed consent has been obtained. This number will serve as the subject’s identifier in the trial as well as in the clinical trial database.

The subject’s data collected in the trial will be stored under this number. Only the Investigator will be able to link the subject’s trial data to the subject via an identification list kept at the site. The subject’s original medical data that are reviewed at the site during source data verification by the Monitor, audits and Health Authority inspections will be kept strictly confidential.

Data protection and privacy regulations will be observed in capturing, forwarding, processing, and storing subject data. Subjects will be informed accordingly, and will be requested to give their consent on data handling procedures in accordance with national regulations.

## Emergency Medical Support and Subject Card

Subjects enrolled in this clinical trial will be provided with Emergency Medical Support cards during their trial participation, which will be furnished by the Sponsor. The Emergency Medical Support card is based on the need to provide clinical trial subjects with a way of identifying themselves as participating in a clinical trial, and subsequently to give health care providers access to the information about this participation that may be needed to determine the course of the subject’s medical treatment.

This service is designed to provide information to health care providers who are not part of the clinical trial. Clinical trial Investigators, who are already aware of the clinical trialprotocol and treatment, have other means of accessing the necessary medical information for the management of emergencies occurring in their subjects.

The first point of contact for all emergencies will be the clinical trial Investigator caring for the affected subject. The Investigator agrees to provide his or her emergency contact information on the card for this purpose. If the Investigator is available when an event occurs, she will answer any questions. Any subsequent action will follow the standard processes established for the Investigators.

In cases where the Investigator is not available, Merck Serono/EMD Serono provides the appropriate means to contact a Sponsor physician. This includes the provision of a 24 hour contact number at a call centre, whereby the health care providers will be given access to the appropriate Sponsor physician to assist with the medical emergency and to provide support for the subject concerned.

## Institutional Review Board

Prior to commencement of the trial at a given site, the clinical trial protocol will be submitted together with its associated documents (e.g.,Subject Information Sheet and Informed Consent Form (ICF), and any other requested documents*)* to the responsible Institutional Review Board (IRB) for its approval. The written approval of the IRB will be filed in the Investigator File and a copy will be filed in the Sponsor’s Trial Master File*.*

The trial must not start at a site before the Sponsor has obtained written confirmation of approval from the concerned IRB. The IRB will be asked to provide documentation of the date of the meeting at which the approval was given, and of the members and voting members present at the meeting. Written evidence of approval that clearly identifies the trial, the clinical trial protocol version and the Subject Information and ICF version reviewed should be provided. Where possible, copies of the meeting minutes should be obtained.

Amendments to the protocolwill also be submitted to the concerned IRB, before implementation in case of substantial changes [(see Section 10.5)](#_Changes_to_the). Relevant safety information will be submitted to the IRB during the course of the trial in accordance with national regulations and requirements.

## Health Authorities

Not applicable

# Trial Management

## Case Report Form Handling

The Investigator or designee will be responsible for entering trial data in the electronic CRF (e-CRF) provided by the Sponsor. It is the Investigator’s responsibility to ensure the accuracy of the data entered in the e-CRFs.

The data will be entered into a validated database, and the Sponsor, or designee, will be responsible for data processing, in accordance with the Sponsor’s, or designee’s, data management procedures. The database lock will occur once quality assurance procedures have been completed. Portable Document Format (PDF) files of the e-CRFs will be provided to the Investigators at the completion of the trial.

## Source Data and Subject Files

The Investigator must keep a subject file (medical file, original medical records) on paper or electronically for every subject included in the trial. This file will contain the available demographic and medical information for the subject, and should be as complete as possible. In particular, the following data should be available in this file: (adapt to trial as necessary)

- Subject’s full name,
- Date of birth,
- Sex,
- Height,
- Weight,
- Medical history and concomitant diseases,
- Prior and concomitant therapies (including changes during the trial),
- Trial identification (Sponsor’s trial number according to clinical trial protocol),
- Date of subject’s inclusion into the trial (i.e. date of giving informed consent),
- Subject number in the trial,
- Subject number (specify as appropriate),
- Dates of the subject’s visits to the site,
- Any medical examinations and clinical findings predefined in the clinical trial protocol,
- All adverse events observed in the subject,
- Date of subject’s end of trial, and
- Date of and reason for early withdrawal of the subject from the trial or from drug, if applicable.

It must be possible to identify each subject by using this subject file.

Additionally, any other documents containing source data must be filed. This includes value listings of subjects’ results from the scheduled laboratory tests and MRI scan images. Such documents must bear at least the subject number and the date when the procedure was performed. Information should be printed by the instrument used to perform the assessment or measurement, if possible. Information that cannot be printed by an automated instrument will be entered manually. Medical evaluation of such records should be documented as necessary and the documentation signed and dated by the Investigator.

Electronic subject files will be printed whenever the Monitor performs source data verification. Printouts must be signed and dated by the Investigator, countersigned by the Monitor and kept in a safe place at the site.

### Hospitalization Records

Subjects may be hospitalized for any reason at the discretion of the Investigator. In case of

hospitalization, the following items will be documented in the Serious Adverse Event Report:

- Reason for hospitalization
- MS relatedness
- Date of admission
- Date of discharge

Each hospitalization constitutes a Serious Adverse Event [(see Section 7.9.1.8)](#_Definition_of_Serious)

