### Adverse Events

#### Adverse Event Definitions

An adverse event (AE) is any untoward medical occurrence in a subject or clinical investigation subject administered a pharmaceutical product, which does not necessarily have a causal relationship with this treatment. An AE can therefore be any unfavorable and unintended sign (including an abnormal laboratory finding), symptom, or disease temporally associated with the use of Rebif®, whether or not considered related to Rebif®.

In cases of surgical or diagnostic procedures, the condition/illness leading to such a procedure is considered as the AE rather than the procedure itself.

In case of a fatality, the cause of death is considered as the AE, and the death is considered as its outcome.

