#### Definition of Serious Adverse Event

A serious adverse event (SAE) is any untoward medical occurrence that at any dose:

- Results in death.
- Is life-threatening.

NOTE: The term “life-threatening” in this definition refers to an event in which the subject is at risk of death at the time of the event; it does not refer to an event that hypothetically might cause death if it were more severe.

- Requires inpatient hospitalization or prolongation of existing hospitalization.
- Results in persistent or significant disability/incapacity.
- Is a congenital anomaly/birth defect.
- Is otherwise considered as medically important.

Important medical events that may not result in death, be life-threatening, or require hospitalization may be considered as SAEs when, based upon appropriate medical judgment, they may jeopardize the subject or may require medical or surgical intervention to prevent one of the outcomes listed in this definition. Examples of such events include allergic bronchospasm requiring intensive treatment in an emergency room or at home, blood dyscrasias or convulsions that do not result in inpatient hospitalization, or the development of drug dependency or drug abuse.

For the purposes of reporting, any suspected transmission of an infectious agent via a Medicinal Product is also considered a SAE and all such cases should be reported in an expedited manner as described in [(see Section 7.9.1.11)](#_Procedure_for_Reporting).

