#### Events that Do Not Meet the Definition of an SAE

Elective hospitalizations to simplify trial treatment or trial procedures (e.g. an overnight stay to facilitate chemotherapy and related hydration therapy application) are not considered as SAEs. However, all events leading to unplanned hospitalizations or unplanned prolongation of an elective hospitalization (e.g., undesirable effects of any administered treatment) must be documented and reported as SAEs.

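### Section 10.2.1 makes every hospitalization an SAE, against the SAE definition it cites and the exclusions in Sections 7.9.1.9 and 7.9.1.10 (low severity)

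*Protocol*

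**What the plan says.** Section 10.2.1 sits under Source Data and Subject Files. It opens with "Subjects may be hospitalized for any reason at the discretion of the Investigator". It then requires that, for a "hospitalization, the following items will be documented in the Serious Adverse Event Report": the reason, MS relatedness, and the admission and discharge dates. It closes with "Each hospitalization constitutes a Serious Adverse Event" and refers to Section 7.9.1.8. It names no exception.

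The safety section has three relevant rules. The subsections of 7.9.1 are unnumbered in the body; the numbers used here come from counting them, and they agree with the protocol's own cross-references to 7.9.1.4, 7.9.1.5, 7.9.1.6, 7.9.1.8 and 7.9.1.11.

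- Section 7.9.1.8 (Definition of Serious Adverse Event) starts from an untoward medical event and lists the criteria that make it serious. One of them is "Requires inpatient hospitalization or prolongation of existing hospitalization".
- Section 7.9.1.9 (Events that Do Not Meet the Definition of an SAE) says that "Elective hospitalizations to simplify trial treatment or trial procedures" "are not considered as SAEs". It keeps as reportable SAEs "all events leading to unplanned hospitalizations or unplanned prolongation of an elective hospitalization".
- Section 7.9.1.10 (Events Not to Be Considered as AEs/SAEs) says that a condition already present at Screening is not an AE unless it becomes more severe or more frequent during the trial.

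**The concern.** The definition in 7.9.1.8 treats hospitalization as a criterion that makes an untoward event serious. Section 10.2.1 treats the admission itself as the SAE, whatever the reason. An admission planned for convenience, or for a stable condition known at Screening, then has two classifications in one protocol.

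The rule has practical effect. SAEs are a listed safety parameter in Section 7.9. SAE status triggers notification within 24 hours under Section 7.9.1.11, and that notification must give the reason for regarding the event as serious and a causality assessment. Neither can sensibly be given where nothing untoward happened. Whichever section the site follows for such an admission, it departs from another.

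An SAP could not settle this, because the question is what the investigator must report, and when.

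**Working it through.** The protocol states no expected number of SAEs or hospitalizations, so there is no planned figure to reproduce. The check sets the rules side by side by type of admission.

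1. **Unplanned admission caused by an untoward event, or unplanned prolongation of an elective stay.** SAE under 10.2.1, 7.9.1.8 and 7.9.1.9. No conflict.
2. **Elective admission to simplify trial treatment or a trial procedure.** SAE under 10.2.1. Not an SAE under 7.9.1.9. Direct contradiction.
3. **Planned admission for a condition present at Screening that has not worsened.** SAE under 10.2.1. Under 7.9.1.10 there is no AE, so under 7.9.1.8 there is no untoward event to be made serious. Contradiction.

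The cross-reference in 10.2.1 does not remove the conflict. It points to 7.9.1.8 but not to 7.9.1.9 or 7.9.1.10, and the sentence it supports is broader than the definition it cites.

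**How likely each type is.** Type 2 is probably empty here. Treatment is self-administered subcutaneous injection after training on Study Day 1. The schedule consists of clinic visits and a telephone call, and no inpatient stay is described. The example in 7.9.1.9 (chemotherapy with hydration) does not fit this trial. Type 3 is the more realistic case: adults aged 18 to 65 are followed from consent to the call four weeks after treatment. The protocol gives no frequency for it.

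**Size.** Inputs: 25 RRMS subjects and 15 healthy controls are planned (Section 5.1.4), and both groups are in the safety population (Section 8.3). If *k* subjects in a group of *n* have only type 2 or type 3 admissions and no other SAE, the two readings differ in SAE incidence by *k/n*.

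- RRMS: 1/25 = 0.040, or 4.0 percentage points per subject.
- Healthy controls: 1/15 = 0.067, or 6.7 percentage points per subject.
- If *k* = 0, the difference is zero.

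These figures assume that planned enrolment is reached. They show how sensitive small groups are to one reclassification. They do not estimate what will happen.

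**The case against.** The case for leaving this alone is fairly strong, and most of it stands.

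- **The class named in 7.9.1.9 is probably empty in an outpatient injection trial.** This stands. What remains is mainly the planned admission for a stable baseline condition.
- **The cited definition already limits the loose sentence.** This is a reasonable way to read 10.2.1, but its text runs the other way: any reason, documentation in the SAE Report, each admission an SAE. A site following those words would not apply the limit.
- **There is one site and one sponsor safety department.** Differences between sites cannot arise. The same site can still classify similar admissions differently, and central receipt does not settle an admission that the site did not report.
- **The broad reading loses no reportable event.** This stands. The worst outcome is a superfluous expedited report and an inflated SAE count.
- **No SAE test or threshold is planned.** This stands too. Section 8.4.4 describes summaries only.

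A reader might infer three stronger points that the protocol does not support. The first is that over-counted admissions would be attributed to Rebif. Causality is graded separately in Section 7.9.1.4, where an admission can be graded unrelated, and healthy controls receive no Rebif. The second is that one or two admissions would be affected in practice; the protocol offers no basis for any number. The third is that Section 7.9.1.1 is a further contradiction. It says "In cases of surgical or diagnostic procedures, the condition/illness leading to such a procedure is considered as the AE rather than the procedure itself". Section 10.2.1 asks for the reason for hospitalization, which records that condition, so the two can coexist.

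**Conclusion.** The contradiction is real and of low severity. It is an internal inconsistency, wrong as written, and not a design choice. For a planned admission with no untoward event, Section 10.2.1 cannot be followed together with Sections 7.9.1.8, 7.9.1.9 and 7.9.1.10.

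The consequence is confined to SAE counts and expedited reporting, and it runs toward over-reporting only. The size is 4.0 points of SAE incidence per affected RRMS subject and 6.7 points per affected healthy control, conditional on that subject having no other SAE. The number of such subjects is unknown and may be zero. The primary MRI endpoint is unaffected.

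**What to change.** Reconcile the passages. One way is to replace the last sentence of Section 10.2.1 with: *Each hospitalization that meets the definition in Section 7.9.1.8 and is not excluded by Sections 7.9.1.9 or 7.9.1.10 constitutes a Serious Adverse Event.* The lead-in about the SAE Report should be limited in the same way.

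Excluded admissions should still be recorded in the e-CRF, with the reason and the admission and discharge dates. The procedure record in Section 6.4.3 asks only for date and reason, so it would need the extra fields, including MS relatedness if that item is to be kept.

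Nothing in the protocol says which section prevails. If the sponsor wants every admission reported as an SAE, the safety sections would have to be changed to say so.

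The cost is a short wording amendment and a few e-CRF fields. Under the suggested wording, unplanned admissions caused by an event remain reportable as they are now.

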## Investigator Site File and Archiving

The Investigator will be provided with an Investigator Site File upon initiation of the trial. This file will contain all documents necessary for the conduct of the trial and will be updated and completed throughout the trial. It must be available for review by the Monitor, and must be ready for Sponsor audit as well as for inspection by Health Authorities during and after the trial, and must be safely archived for at least 15 years (or per local requirements or as otherwise notified by the Sponsor) after the end of the trial. The documents to be thus archived include the Subject Identification List and the signed subject Informed Consent Forms. If archiving of the Investigator Site File is no longer possible at the site, the Investigator must notify the Sponsor.

All original subject files (medical records) must be stored at the site (hospital, research institute, or practice) for the longest possible time permitted by the applicable regulations, and/or as per ICH GCP guidelines, whichever is longer. In any case, the Investigator should ensure that no destruction of medical records is performed without the written approval of the Sponsor.

## Monitoring, Quality Assurance and Inspection by Health Authorities

This trial will be monitored in accordance with the ICH Guideline on Good Clinical Practice (ICH Topic E6, 1996). The site Monitor will perform visits to the trial site at regular intervals.

Representatives of the Sponsor’s Quality Assurance unit or a designated organization, as well as Health Authorities, must be permitted to inspect all trial-related documents and other materials at the site, including the Investigator Site File, the completed e-CRF, the drug(s), and the subjects’ original medical records/files.

The clinical trial protocol, each step of the data capture procedure, and the handling of the data, including the final clinical trial report, will be subject to independent Quality Assurance activities. Audits may be conducted at any time during or after the trial to ensure the validity and integrity of the trial data.

